### Model development process

#### Predictors and outcomes

Based on demographics, clinical, medical management, patient characteristics, CHA_2_DS_2_-VASc score, HAS-BLED score, the expertise of treating physicians, NOAC availability, and clinical relevance, we can identify the variables potentially related to inappropriate NOAC use. Variables above will be extracted from the medical records in each participating institution using an *a priori* designed form. The target outcome will be NOAC inappropriateness. Patients with more than 30% missing data will be excluded. For patients with partially missing data, the Random Forest (RF) algorithm will be used for data-level computation.

#### Data separation and feature filtering

In this process, the data will be randomly divided into training and test sets in a ratio of 8:2, which will be used for the model establishment and verification, respectively. Feature selection will be performed using the Sequence Forward Selection algorithm based on RF. For each group, the algorithm will search from the empty set and subsequently add one variable to the feature subset each time to achieve an optimal performance, which is measured by the F1 score.

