### Sample size calculation

This study is designed as a multicenter cross-sectional study. Assuming that each institution can treat 300–500 patients with AF per year, patients over 75 years old account for 20–30% and the rate of NOAC use is ~50–70%, with a 2% error range and 95% confidence interval (CI). The drop-out rate is not considered in the calculation as the primary outcomes will be evaluated during hospitalization; the drop-out rate is expected to be very low. To get a representative result, we calculated that a sample size of 1,500 patients would be sufficient. Since this is an event-driven study (the rate of inappropriate NOAC use), the total number of patients may change as necessary according to the cumulative number of target events.

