### Strengths and limitations

The main strengths of this study are believed to be as follows: First, we will include data from a national, comprehensive, and diversified cohort of older patients with AF and will perform in-depth phenotyping of NOAC use to help refine best practices for older adults with AF. Second, most studies evaluating the appropriateness of NOAC primarily focus on dosage in the general population, while our study will evaluate the rationale of NOAC decision-making for older adults from multiple perspectives: patient factor (patients' demographics and categories of treating physicians) and institution layer (the availability of certain NOACs in that center). Additionally, this study will build the first prediction model to predict the inappropriateness of NOAC in older Chinese patients with AF.

Inevitably, this study has some inherent limitations. First, due to the inherent restriction placed by its design, this study will not evaluate the outcomes of older adults with AF treated with inappropriate anticoagulation therapy, nor will there be a follow-up for efficacy evaluation. Nevertheless, its primary purpose is to establish a reliable prediction model in older adults with NVAF receiving NOAC. Second, data will be dependent on the quality of medical record extraction, so that residual and unmeasured covariates among the associated variables may influence the results, even after strict measurement and recording of crucial variables and avoidance of confounding factors. Last, the prediction model needs independent validation in other cohorts to establish its utility for clinical use, not least in older outpatients taking NOACs.

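### One random 20% hold-out is a valid but inefficient check of the prediction model: at 1,500 patients it fixes the AUROC only to about ±0.05 to ±0.08, where cross-validation on all patients would give about ±0.024 to ±0.036

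*Protocol article*

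**What the plan says.** Under Data separation and feature filtering, "the data will be randomly divided into training and test sets in a ratio of 8:2", the larger part for building the model and the smaller for verifying it. The article names no cross-validation, bootstrap, repeated split, or split by centre or period. Under Machine learning model establishment, evaluation, and interpretation, logistic regression, random forest, support vector machine, several boosting methods and TabNet are compared on five measures, and models are selected by AUROC.

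The model is not a side product. It is one of the four primary outcomes, and Strengths and limitations says of the study that "its primary purpose is to establish a reliable prediction model in older adults with NVAF receiving NOAC". The same section leaves independent validation to other cohorts.

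Sample size calculation concludes that "a sample size of 1,500 patients would be sufficient" but adds that "the total number of patients may change as necessary according to the cumulative number of target events". No expected AUROC is given, and no expected rate of inappropriate use is given as a design input. The Discussion cites one cohort in which nearly a quarter of older adults received a potentially inappropriate dose, and another with about 60% label adherence, which implies about 40% non-adherence.

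**The concern.** The hold-out is the only check of the model that the article describes, and it uses one fifth of the patients. The precision of every reported performance measure is therefore set by about 300 patients and, for precision, recall and F1, by perhaps 75 to 120 events. The other four fifths contribute nothing to the performance estimate.

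Because the split is drawn once, another equally legitimate random draw from the same patients could give a noticeably different AUROC. What is at stake is how firmly the study can state the performance of its main product, when a standard alternative would use the same data better at no cost in patients.

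**Working it through.** **Inputs.** Total N = 1,500 (Sample size calculation). Split 8:2 (Data separation and feature filtering). Event rates of 25% and 40% are anchors from studies cited in the Discussion, not design assumptions. A rate of 20% is added as a lower value. AUROC 0.70 to 0.80 is assumed.

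**The plan's own figure.** For a half-width of 2 percentage points at 95% confidence, n = 1.96² p(1−p)/0.02². This gives 1,537 at p = 20%, 1,801 at 25%, 2,305 at 40% and 2,401 at 50%. Only p of about 19–20% comes close to 1,500, and the article does not state the p it used, so the figure cannot be reproduced. That is a separate matter; here only the planned N is needed.

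**Size of the two sets.** Test: 0.20 × 1,500 = 300. Training: 1,200. Test events: 300 × 0.25 = 75; 300 × 0.40 = 120; 300 × 0.20 = 60.

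**Precision of the AUROC.** Hanley–McNeil, with A the AUROC, n₁ events and n₀ non-events:

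SE² = [A(1−A) + (n₁−1)(q₁−A²) + (n₀−1)(q₂−A²)] / (n₁n₀), where q₁ = A/(2−A) and q₂ = 2A²/(1+A).

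For A = 0.70: q₁ = 0.5385, q₂ = 0.5765, A² = 0.49.

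- Test set, 75 events and 225 non-events: SE² = (0.21 + 74 × 0.0485 + 224 × 0.0865)/16,875 = 0.00137, so SE = 0.037 and the half-width is 1.96 × 0.037 = 0.073.
- All patients, 375 and 1,125: the same formula gives SE = 0.0165 and half-width 0.032.

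95% half-widths over the range:

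| Event rate | Assumed AUROC | n = 300 | n = 1,500 |
|---|---|---|---|
| 20% | 0.70 | ±0.080 | ±0.036 |
| 20% | 0.80 | ±0.071 | ±0.032 |
| 25% | 0.70 | ±0.073 | ±0.032 |
| 25% | 0.80 | ±0.064 | ±0.029 |
| 40% | 0.70 | ±0.062 | ±0.028 |
| 40% | 0.80 | ±0.053 | ±0.024 |

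The range is ±0.053 to ±0.080 with the hold-out and about ±0.024 to ±0.036 if all patients contribute. The ratio is about √5 = 2.24, as expected from five times the patients. The right-hand column approximates what cross-validation achieves, since it treats the out-of-fold predictions as one sample of 1,500.

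**Dependence on the draw.** Simulated data had 1,500 patients, 15 candidate predictors, logistic regression, mean AUROC about 0.70 and nominal event rates of 25% and 40%, with 300 random 8:2 splits on each of eight datasets. Re-splitting the same patients gave an AUROC standard deviation of 0.027 to 0.031, with a 95% range 0.11 to 0.12 wide. For 10-fold cross-validation the standard deviation across random partitions was about 0.003. That 0.003 measures only dependence on the partition; the sampling uncertainty remains that of the right-hand column.

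**If N changes.** The article's own flow figures give, for 31 institutions and one year, between 31 × 300 × 0.20 × 0.50 = 930 and 31 × 500 × 0.30 × 0.70 = 3,255 eligible patients, hence test sets of 186 to 651. At 25% events and AUROC 0.70 the half-width would be 0.073 × √(300/186) = 0.093 or 0.073 × √(300/651) = 0.050.

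**Choice of resampling method.** Bootstrap optimism correction was checked as an alternative. In a simulation with 1,500 patients, about 25% events and a 200-tree random forest, the true AUROC was 0.63 to 0.64, the apparent AUROC 1.00 and the corrected value 0.94. A second check with a learner that memorises its training data gave 0.95 against a true 0.65. Most of the original sample has already been seen by each bootstrap model, so the correction removes far too little optimism.

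**The case against.** The strongest reply is that a held-out random split is a legitimate, unbiased internal check, and that resampling is more efficient rather than the correction of an error. That stands. It can be added that a journal article condenses a fuller plan, which may specify resampling within the training set, a seed or repeated splits. Resampling inside the training set would help tuning but would leave final verification on the same 300 patients. The article states the single division as its method, so the comment is on a stated choice and not on an omission.

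Several stronger readings are tempting, and the documents do not support them:

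- A reader might infer that development is starved of data. At 25–40% events the 1,200 training patients carry 300 to 480 events. In a simulation with 15 predictors and logistic regression, developing on 1,500 instead of 1,200 raised the true AUROC by only 0.002. The article speaks of predicting in the entire cohort, and nothing rules out a final refit on everyone.
- A reader might infer that the split should go because it says nothing about new hospitals. It does not show transport, but neither does ordinary cross-validation, and the article already says that validation in other cohorts is needed.
- A reader might infer that verification cannot separate a useful model from a weak one. The article sets no threshold for either. At 25% events an observed 0.70 has an interval of about 0.63 to 0.77, which is wide but excludes 0.50.
- A reader might treat the interval and the dependence on the draw as two errors to be added. They largely describe the same test-set noise.

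**Conclusion.** The point holds as one of precision and efficiency, not of bias. With 1,500 patients, 20–40% events and a true AUROC of 0.70–0.80, the hold-out gives a 95% half-width of about ±0.05 to ±0.08, and the reported value shifts with the random draw. Using all patients through cross-validation would more than halve that, to about ±0.024 to ±0.036.

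No single figure such as ±0.07 should be read as a property of the plan. It applies at about 25% events and an AUROC of 0.70–0.75, and neither is a design assumption in the article. The 300 is conditional as well: the sample size may change with the number of events, and exclusions for missing data could lower it. Since the model is described as the study's primary purpose and the remedy needs no further patients, the change is worth making.

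**What to change.** Under Data separation and feature filtering, replace the single 8:2 division with repeated 10-fold cross-validation on all patients. Imputation, feature selection, tuning and model choice should be repeated inside every fold, so that no step sees the patients on whom it is judged. Report the cross-validated AUROC with a 95% interval that reflects sampling error, not merely the spread across repeats. Fit the final model on all patients.

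Do not use bootstrap optimism correction for the random forest or boosting models. Keep the existing statement that independent validation in other cohorts is still needed.

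The cost is a change of wording and more computing time, which will be noticeable because the random-forest forward selection and all the listed algorithms are rerun in each fold. No additional patients or data are required.

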#### Machine learning model establishment, evaluation, and interpretation

Both linear and non-linear machine learning models will be applied to the sets, which include logistic regression, RF, support vector machine, gradient boosting tree (such as XGBoost, LightGBM, Adaboost, and Catboost), and attentive interpretable tabular learning (TabNet). The prediction performance of all models will be evaluated through five measures (area under the receiver operating characteristics [AUROC] curve, precision, recall, F1 score, and accuracy). The acceptably performing machine learning models will be selected according to AUROC. Next, we will calculate the importance scores of the features using the above-chosen algorithms. Features with higher importance scores are more closely related to the accurate prediction of NOAC inappropriate use. Finally, features ranked in the top 50% based on normalized importance scores in selected models will be determined as major predictors and depicted in radar plots.

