Previous studies report relevant risk factors for inappropriate NOACs use. In the SAGE-AF (Systematic Assessment of Geriatric Elements in Atrial Fibrillation) cohort, a potentially inappropriate NOAC dose was prescribed to nearly a quarter of older adults. This stemmed from patients being older, having poor renal function, and higher CHA_2_DS_2_-VASc scores (16). Another Korean study found that NOAC label adherence was approximately 60%, and the risk factors of NOAC under-dosing were independently related to old age (≥75 years), female sex, lower body weight (< 60 kg), renal impairment (CrCl < 50 ml/min), hypertension, previous stroke/transient ischemic attack (TIA)/thromboembolic events, bleeding history, and concomitant dronedarone or antiplatelet agent use (29). In the ORBIT-AF II registry (18), compared with those whose NOAC dose was appropriately reduced, patients accepting inappropriate dose reductions were younger and had lower bleeding risk scores. Physician assessment may have a strong impact on inappropriate NOAC dosing; however, there may also be drug-specific factors. In Mainland China, information on practice patterns of NOAC administration and the use of NOACs for licensed indications in older patients remains scarce.

Currently, few studies have focused attention on the prediction model of the risk factors of NOAC inappropriateness in elderly patients with AF. Considering that inappropriate NOACs doses are prescribed to a fair percentage of older patients with AF, with most being under-dosed, the development of a practical prediction model with reliable predictability is of great value. To our knowledge, this will be the first study to establish a feasible prediction model for predicting inappropriate NOAC use in older Chinese patients with AF. In the prediction model of probabilistic estimation, we will combine the above independent predictors and the risk factor variables from previously published research. Accordingly, we believe that the prediction model could be applied as a simpler and more effective tool for clinical decision-making for elderly patients with AF.

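### Forward selection scored by F1 at a class cut-off can admit continuous noise and delay or miss real binary risk factors when inappropriate use is a minority outcome

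*Protocol article*

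**What the plan says.** The section on data separation and feature filtering states that "the data will be randomly divided into training and test sets in a ratio of 8:2". It then fixes the method: "Feature selection will be performed using the Sequence Forward Selection algorithm based on RF". The search starts with no variables, and each step is meant to "add one variable to the feature subset each time to achieve an optimal performance, which is measured by the F1 score".

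The next section, on machine learning models, uses another measure to choose among the fitted models: "The acceptably performing machine learning models will be selected according to AUROC". F1 appears there as one of five performance measures.

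The Statistical analyses section adds a separate entry rule. A variable needs a univariate p-value of at most 0.05 and published plausibility to enter the final prediction model. The article does not say how this rule combines with the forward search.

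No inappropriate-use rate is planned. The sample size section gives only a proportion for uptake, "the rate of NOAC use is ~50–70" per cent. The Discussion reports that in one cohort "a potentially inappropriate NOAC dose was prescribed to nearly a quarter of older adults". It also cites a Korean study with about 60% label adherence, which implies about 40% non-adherence.

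**The concern.** F1 counts true positives among patients who are classified as inappropriate. If the forest classifies a patient as inappropriate only when the predicted risk exceeds 0.5, a variable that moves risk from 0.2 to 0.4 classifies nobody and earns nothing, however real the effect. A continuous variable behaves differently. Fully grown trees can split it down to single patients and so produce positive calls even when it carries no information. At the first step the score can then rank continuous noise above a real binary factor.

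This matters because many candidates in the data collection table are binary: sex, urban or rural residence, comorbidities, procedures, fall history, co-medication, cardiologist or not. Others are continuous: age, weight, creatinine, haemoglobin, bilirubin, creatinine clearance. As the sections are ordered, the search comes before the machine-learning models and the list of major predictors drawn from them. The prediction tool, primary outcome (d), is what is exposed.

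**Working it through.** **Inputs.** The planned sample is stated as "we calculated that a sample size of 1,500 patients would be sufficient"; 80% of it gives 0.8 × 1,500 = 1,200 training patients. Event rates are 25% and 1 − 0.60 = 40%, both from studies cited in the Discussion. Odds ratios (OR), prevalences and forest settings (cut-off 0.5, no class weights, fully grown trees) are assumptions.

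The plan has no figure of its own on this point to reproduce.

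**Step 1: risks for one binary factor.** Let p be the event rate, q the prevalence, and r0 and r1 the risks without and with the factor. Then p = q·r1 + (1 − q)·r0, and OR = [r1/(1 − r1)] / [r0/(1 − r0)]. For p = 0.25 and q = 0.30:
- OR 2: r0 = 0.209, r1 = 0.346
- OR 3: r0 = 0.184, r1 = 0.404

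Both risks are below 0.5, so nobody is classified positive, there are no true positives, and F1 = 0. A useless binary variable gives the same classification and hence the same score.

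**Step 2: how strong must the factor be?** Set r1 = 0.5. Then r0 = (p − 0.5q)/(1 − q), and the threshold is OR = (1 − r0)/r0. For p = 0.25 and q = 0.30, r0 = 0.10/0.70 = 0.143 and OR = 6.0.

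| Prevalence | OR needed at 25% | OR needed at 40% |
|---|---|---|
| 10% | 3.5 | 1.6 |
| 20% | 4.3 | 1.7 |
| 30% | 6.0 | 1.8 |
| 50% | not possible | 2.3 |

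**Step 3: why noise scores.** If positive calls are made at about rate p and are unrelated to outcome, precision = p and recall = p, so F1 = p. This predicts 0.25 and 0.40.

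**Step 4: simulation, one variable at a time.** Candidates were 4 real binary factors (prevalence 20–50%), 2 real continuous variables (OR 1.5 per SD), 4 continuous noise and 2 binary noise variables. There were 1,200 patients, 3-fold cross-validation, 50 trees, and 5 to 6 runs per setting. Entries are mean F1, real binary against continuous noise.

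| Setting | OR 2 | OR 3 |
|---|---|---|
| 25%, default, fine-grained values | 0.000 vs 0.244 | 0.000 vs 0.251 |
| 25%, default, rounded to 0.1 SD | 0.000 vs 0.040 | 0.000 vs 0.037 |
| 25%, minimum leaf 20, rounded | 0.000 vs 0.002 | 0.000 vs 0.000 |
| 25%, class-weighted, rounded | 0.375 vs 0.329 | 0.418 vs 0.338 |
| 40%, default, fine-grained | 0.277 vs 0.401 | 0.457 vs 0.400 |
| 40%, default, rounded | 0.304 vs 0.275 | 0.453 vs 0.259 |

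At 40% with fine-grained values, noise scored higher in 77% of pairs at OR 2 and 24% at OR 3. A separate simulation of one factor (30% prevalence) against one noise variable, with 5-fold cross-validation and 100 runs, gave 59% and 0%.

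Scored by AUROC, the default forest at 25% (rounded values) gives real binary factors 0.558 against 0.494 for noise at OR 2, and 0.590 against 0.502 at OR 3.

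**Step 5: the search itself.** At 25% with fine-grained values, the variable with the highest F1 was a real continuous one in 8 of 12 runs and noise in 4. In four six-step paths at 25% (default, rounded), 2 or 3 of the 4 real binary factors entered, the first at step 3 or 4. Between one and three noise variables entered each path. These paths were forced to six steps, so some noise would be expected under any score, and no AUROC path was run on this candidate set.

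**The case against.** The strongest reply is that the effect comes from settings the article does not state. Cut-off, class weights, tree depth and F1 averaging are details that a full protocol or SAP normally holds, and their absence from an article is no fault. The reply stands as a limit on size. Class weighting reverses the average order. A minimum leaf of 20 removes nearly all the noise advantage, although real binary factors stay at zero. Weighted-average F1 also reverses the order (0.645 vs 0.634 at OR 2; 0.640 vs 0.631 at OR 3, in 10 runs at 25%), while macro-averaged F1 does not. Even so, under any averaging, a real and a useless binary factor that both classify nobody positive get the same score.

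A reader might go further in four ways that the documents do not support:

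- **That 25% is the study's own rate.** It is a cited result about dose only. This study's outcome also covers indication, choice of agent and contraindication, and the other cited study implies about 40%.
- **That the search must start from the wrong predictors.** Zero credit applies mainly to the empty-set step. Age, weight and creatinine clearance enter the dosing table, so real continuous predictors are likely. In a three-step search without any, F1 picked noise first in 8 of 8 runs and AUROC in 0 of 8. With them, the figure for F1 was 4 of 12.
- **That primary outcome (c) is damaged.** Risk factors come mainly from the logistic regression, which does not depend on this search as written.
- **That F1 here contradicts AUROC later.** Different measures at different stages are allowed. The later use of AUROC only shows that a cut-off-free measure is already in the plan.

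The p-value and plausibility rule is also a real safeguard. Pure noise passes p ≤ 0.05 about 5% of the time and would still need published support. The rule may remove some noise, but it cannot recover a factor that the search never selected.

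**Conclusion.** The concern holds in limited form. F1 at a class cut-off is a poor score for adding variables when the outcome is a minority one. At a 25% rate with default forest settings, a single binary factor of OR 2 to 3 and 30% prevalence gets exactly 0 at the first step, while fine-grained continuous noise gets about 0.25. At 40%, noise is about level or ahead at OR 2 and behind at OR 3. With coarsely rounded noise at 25%, the noise score falls to about 0.04.

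The zero for binary factors follows from arithmetic once the rate and the 0.5 cut-off are assumed. The noise scores rest on simulation with few runs, assumed effect sizes and a newer scikit-learn release than the one planned. The supported conclusion is that the rule can admit continuous noise and can delay or miss real binary factors in the prediction tool, primary outcome (d).

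**What to change.** In the section on data separation and feature filtering, replace F1 as the forward-selection score with cross-validated AUROC or log-loss, computed within the training set only. AUROC is already the measure used to choose among models. Keep F1 among the reported performance measures. In the same edit, say how the search combines with the p-value and plausibility rule in the Statistical analyses section.

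If F1 is kept for selection, fix the class weights, cut-off and averaging in advance.

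The main change costs one line of text and one scoring argument in the code. The only downside is that the selected set is no longer tuned to F1.
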